### Endpoints

#### Primary endpoint

Postoperative complication rates within 30 postoperative days: Postoperative complication rates are calculated as the total number of postoperative complication cases per total operation cases.

Clavien-Dindo grade of postoperative complications in 180 postoperative days: The Clavien-Dindo grade of postoperative complications is evaluated. Only grade III or higher postoperative complications are used for this analysis.

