### Sample size determination

We determined the sample size for this study according to the real clinical experience of the PI, without statistical calculation, to explore the safety and effectiveness of the robotic surgical system and derive clinical outcomes from the procedures. The main institution performed 4038 cases of breast surgery and 746 cases of mastectomy and IBR (18.5%) between 2016 and 2018, including 86 RRMs (86/746, 11.5%). The iBRA study reported the uni- or bilateral RRMs accounted for 34.8% of mastectomies [53]. The mean value of the RRM rate between the main institution and the iBRA study was 23.15%. We estimated an approximate sample size of 11.5% for the main institution and 23.15% for the other institutions.Planned enrollment is 2000 total patients across the conventional, endoscopic, and robotic groups.

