### Statistical analyses

We have categorized three study sets: Conventional vs. endoscopic, conventional vs. robotic, and conventional vs. endoscopic and robotic. Additionally, subgroup analyses of a randomized registry trial will be conducted to compare the surgical and oncologic outcomes between the conventional and minimally invasive (endoscopic and robotic) groups. Primary and some secondary outcomes (postoperative complications, the satisfaction of patients and surgeons, and the cost-effectiveness evaluation) and other categorical variables will be examined by the chi-square test or Fisher's exact test. Continuous variables will be examined by t-testing or ANOVA and Mann–Whitney testing or Kruskal–Wallis testing, if needed. The other secondary outcomes (RFS, OS, and cancer incidence rates in 5 years) will be examined using Kaplan–Meier plots and log-rank testing. No imputation will be performed for subjects who have missing data due to dropping out of the study. Data relating to major protocol non-adherence due to patients dropping out of the study will be excluded from the analysis population.

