## Discussion

This study will provide evidence about the surgical outcomes, oncologic outcomes, and patient satisfaction with RNSM and ENSM, compared with CM.

This prospective cohort study has some advantages over previous retrospective studies conducted in a single center or with a single surgeon. The sample size of the study is larger than previously published studies of RNSM. Additionally, our protocol will collect large-scale PRO data about cosmesis after RNSM. The participation of many surgeons from multiple institutions will allow us to observe the effects of different surgeons or institutions on the clinical outcomes of the surgical procedures. In Korea, an increasing number of breast surgeons has been performing RNSM because of active educational programs and systematic research activities. Therefore, the involvement of many skilled surgeons will produce accurate clinical outcomes for the procedures. However, because this is not a randomized controlled trial, selection bias might still occur in determining the surgical modality for each subject. To overcome that limitation and secure the surgical and oncologic outcomes from a new, innovative surgical procedure, we are planning a randomized controlled trial for the near future.

Through this study, we wish to confirm that minimally invasive breast surgery can be considered as a standard treatment for women with breast cancer and as a preventive treatment for women with a high risk of pathogenic variants.

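### The stated chi-square and log-rank tests ignore surgeon and institution, so p-values for the method contrasts may be too small to the extent that surgeons differ in their mix of techniques

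*Protocol article*

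**What the plan says.** The Statistical analyses section of the protocol article names the tests. Complications, satisfaction, cost-effectiveness and "other categorical variables will be examined by the chi-square test" or Fisher's exact test. Recurrence-free survival (RFS), overall survival (OS) and five-year cancer incidence "will be examined using Kaplan–Meier plots and log-rank testing". The section mentions no surgeon or institution term, stratification, random effect, frailty or clustered variance.

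The Discussion says that having many surgeons at several institutions "will allow us to observe the effects of different surgeons or institutions on the clinical outcomes of the surgical procedures". It also states that the study is not randomised and that selection bias may enter through the choice of modality.

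On size, the Sample size determination section says "Planned enrollment is 2000 total patients across the conventional, endoscopic, and robotic groups". That number was set "without statistical calculation, to explore the safety and effectiveness of the robotic surgical system". The article gives no number of surgeons, no ICC and no technique share per surgeon.

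**The concern.** Patients of one surgeon tend to share an outcome level because skill, case selection and aftercare are common to them. The chi-square, Fisher and log-rank tests ignore this. It matters for a comparison of methods only if method is also associated with surgeon.

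The article makes that association plausible. Its Background describes endoscopic and robotic mastectomy as work done by specialised surgeons, few of them in the robotic case. The Discussion describes growing uptake of the robotic procedure. Nothing in the design balances method within surgeon.

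Two things are then at stake:
- **Error rate.** The stated standard errors may understate the uncertainty of the contrasts on both primary endpoints and on survival.
- **Attribution.** A few surgeons with unusually high or low complication rates who favour one technique can create an apparent difference between techniques.

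Separately, the surgeon and institution effects announced in the Discussion are delivered by no stated analysis.

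**Working it through.** **1. The plan's own calculated figure.** The only size with a statistical calculation is the 112-patient matched subset (Pre-specified subgroup analysis). Inputs: reference rate 0.348, robotic rate 0.171, margin 0.05, one-sided alpha 0.025, power 80%.
- Distance to the margin: 0.05 + 0.348 − 0.171 = 0.227.
- Variance: 0.348×0.652 + 0.171×0.829 = 0.3687.
- n per group = 0.3687 × (1.960 + 0.842)² / 0.227² = 56.15.

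Exact binomial enumeration at 56 per group (112 in total) gives alpha 0.0265 and power 80.04%, as stated. The figure reproduces, and it too assumes independent patients. The 2000 has no calculation behind it, so no design effect is built into it.

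**2. Inputs for the clustering check.** From the article: N = 2000. Assumed, because the article gives none of them: J = 20 or 40 surgeons with equal caseload m = 2000/J, an ICC, a distribution of technique share, and no true method effect.

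**3. Hand approximation.** The variance inflation is about 1 + (m − 1) × ICC × r. Here r is the variance of the technique share between surgeons divided by s(1 − s), with s the mean share. The true error of a nominal 5% test is about 2 × [1 − Φ(1.96/√inflation)].
- Same mix for every surgeon: r = 0, no inflation.
- Shares uniform from 0 to 100%: r = (1/12)/(1/4) = 1/3.
- Each surgeon uses one technique only: r = 1.

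Example with 20 surgeons, ICC 0.05 and uniform shares: 1 + 99×0.05/3 = 2.65; √2.65 = 1.63; 1.96/1.63 = 1.20; error about 0.23.

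**4. Simulation of the chi-square test** (20% event rate, 4000 null runs per cell, Monte Carlo SE about 0.003 at 5%):

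| Surgeons | ICC | Same 50:50 mix | Mild variation, Beta(5,5) | Uniform shares | One technique each |
|---|---|---|---|---|---|
| 20 | 0.01 | 0.049 | 0.057 | 0.089 | 0.163 |
| 20 | 0.02 | 0.044 | 0.067 | 0.121 | 0.257 |
| 20 | 0.05 | 0.038 | 0.098 | 0.220 | 0.416 |
| 40 | 0.01 | 0.043 | 0.051 | 0.067 | 0.094 |
| 40 | 0.02 | 0.048 | 0.055 | 0.083 | 0.166 |
| 40 | 0.05 | 0.042 | 0.069 | 0.139 | 0.293 |

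**5. A second model.** This uses normal surgeon effects on the logit scale, a 25% event rate, and shares from Beta(2,3) (moderate preference) or Beta(0.8,1.2) (strong preference). ICC = SD²/(SD² + π²/3): SD 0.3 gives 0.09/3.38 = 0.03 and SD 0.5 gives 0.25/3.54 = 0.07.
- 20 surgeons: 0.081 and 0.112 at SD 0.3; 0.145 and 0.201 at SD 0.5.
- 40 surgeons: 0.070 and 0.081 at SD 0.3; 0.098 and 0.135 at SD 0.5.
- Same mix for all: 0.045 to 0.054.

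**6. Log-rank** (assumed 10% events in five years): rejection about 7 to 16% with 20 surgeons, 6 to 10% with 40, and 5 to 6% with the same mix.

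**The case against.** **The direction is conditional.** A reader might infer that the p-values are too small in any case. They are not: with the same mix for every surgeon the tests are nominal or slightly conservative, and with mild variation the inflation is small. This stands.

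**Few surgeons, and method fixed by surgeon, are not in the text.** A reader might also infer that a small number of surgeons operate, each with a set technique. The article speaks of many surgeons without a count, describes modality as determined for each subject, and requires robotic training of its surgeons. One surgeon may therefore use several techniques, and the one-technique column above is a bound, not an expectation. This stands. It does not make the shares equal.

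**The size rests on assumptions.** Surgeon count, ICC, shares and event rates are all assumed. Two of the three planned comparisons leave out one group, so fewer women per surgeon enter and the inflation shrinks at a given ICC. The article states no 5% level for the cohort contrasts and calls the study exploratory. All true, although its closing aim is to confirm minimally invasive surgery as a possible standard treatment.

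**The full analysis plan may handle it.** It may, but the tests are named here. A clustered model would replace a published choice, not fill in a detail.

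**This is partly confounding.** Surgeons who favour one method also shift the estimate, and clustered variance alone does not remove that. This stands and shapes the fix.

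The 30-day rate is counted per operation ("Postoperative complication rates are calculated as the total number of postoperative complication cases per total operation cases"). Two operations on one woman would add a further correlation, which is a separate matter.

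**Conclusion.** The point holds in conditional form. The stated tests assume independence and contain no surgeon or institution term, in a non-randomised comparison whose own Discussion expects to observe surgeon and institution effects. To the extent that technique share differs between surgeons, standard errors and p-values may be too small and surgeon differences may be read as method differences.

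With 20 to 40 surgeons, ICC 0.01 to 0.07 and moderately to widely varying shares, a nominal 5% chi-square test rejects in roughly 7 to 22% of null runs. With mild variation it is about 5 to 10%, and with equal shares about 4 to 5%. The log-rank inflation is smaller. The article does not fix where in this range the study lies. What it does fix is a method that is safe only in the equal-share case, and a promise that no stated analysis keeps.

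**What to change.** Change the Statistical analyses section as follows.
- **Complications:** use a logistic or risk-difference model for method with a random intercept for surgeon (or surgeon within institution). The alternative is variance clustered on surgeon with a small-sample correction.
- **RFS and OS:** use a Cox model with surgeon frailty or surgeon-clustered variance.
- **Chi-square, Fisher and log-rank:** keep as descriptive.
- **Reporting:** give the number of surgeons, the technique share by surgeon and the between-surgeon SD. This also supplies what the Discussion promises.

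Prefer the model with a surgeon term. Clustered variance alone widens the interval but leaves the point estimate confounded by surgeon.

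The cost is a short change to the text and somewhat wider intervals. A surgeon identifier must be in the dataset; the data items listed in Methods/Design do not mention one, but observing surgeon effects already requires it.

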The Korea Robot-Endoscopy Minimal Access Breast Surgery Study Group (KoREa-BSG) has been established to evaluate, standardize, and teach this state-of-the-art procedure. Previously, the KoREa-BSG retrospectively analyzed the initial experiences of surgeons and showed that RNSM is technically feasible and reliable, with a short learning curve [19]. Therefore, to obtain a high level of evidence, we designed a multicenter prospective exploratory cohort study entitled Mastectomy with Reconstruction Including Robotic Endoscopic Surgery (MARRES) to collect data on surgical outcomes, PROs, and oncologic outcomes (Protocol serial numbers: KoREa-BSG 03 and KBCSG-23).

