#### Secondary endpoints

Recurrence-free survival (RFS) in 5 postoperative years: RFS events include locoregional recurrence, distant recurrence, and death by any cause. Contralateral breast cancer and a second primary malignancy are considered to be censored data.

Cancer incidence rate in 5 postoperative years: Cancer incidence rate for those who underwent a prophylactic mastectomy.

Patient satisfaction with reconstruction results preoperative (baseline) and 6 to 12 postoperative months: Reconstruction module with pre- and postoperative scales for satisfaction with the abdomen, as assessed by BREAST-Q version 2.0. (This scale should be completed only by patients who have had reconstruction using a TRAM flap or DIEP flap. Otherwise, it is skipped.) Satisfaction with the back, as assessed by BREAST-Q version 2.0. (This scale should only be completed by patients who have had reconstruction using an LD flap. Otherwise, it is skipped.) Satisfaction with implants, as assessed by BREAST-Q version 2.0. (This scale should only be completed by patients who have had reconstruction using implants. Otherwise, it is skipped.) In all scales, higher scores reflect better outcomes.

Surgeon's satisfaction with surgery within 6 postoperative months: Assessed using scoring criteria for cosmetic assessment [52], response options (overall symmetry, postoperative scar, NAC symmetry, etc.), and range (0–10). Higher scores reflect better outcomes.

Evaluation of the cost-effectiveness of the definitive surgery according to the surgical method: Assessed by conducting a patient’s survey 6 months to 1 year after the last surgery. This evaluation uses the EuroQol five-dimension scale, Korean version questionnaire. In all scales, higher scores reflect better outcomes.

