### Pre-specified subgroup analysis

Because of the long duration and expensive cost of a randomized trial, we will extract random patients from our prospective cohort and conduct subgroup analyses as a randomized registry trial. In a previous study, the rates of grade III complications in the reference group and the robotic group were 34.8% and 17.2%, respectively. For the comparison of complication rates among different surgical methods, the required sample size was calculated as 112 (1:1 random match) according to the method used in a randomized registry trial previously introduced to detect a non-inferiority margin difference, which achieved 80% power between the group proportions of 0.0500. The robotic group proportion is assumed to be 39.8% under the null hypothesis of inferiority. The power was computed for the case in which the actual robotic group proportion is 17.1%. The test statistic used is the one-sided Z test (unpooled). The significance level of the test was targeted at 0.0250. The actual significance level achieved by this design is 0.0265.

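### Log-rank difference tests alone cannot support the oncologic part of the hoped-for standard-treatment conclusion, and the protocol article gives no margin or confidence bound for it

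*Protocol article*

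**What the plan says.** All references are to the protocol article.

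- **Statistical analyses** gives the method for the time-to-event outcomes: "The other secondary outcomes (RFS, OS, and cancer incidence rates in 5 years) will be examined using Kaplan–Meier plots and log-rank testing". No hazard ratio, interval, margin or reading rule goes with it.
- The same section adds that "subgroup analyses of a randomized registry trial will be conducted to compare the surgical and oncologic outcomes" between conventional and minimally invasive surgery.
- **Pre-specified subgroup analysis** sizes that exercise on one endpoint: "For the comparison of complication rates among different surgical methods, the required sample size was calculated as 112 (1:1 random match"). Here there is a 0.05 margin, a null hypothesis of inferiority and a one-sided test.
- **Sample size determination** states: "Planned enrollment is 2000 total patients across the conventional, endoscopic, and robotic groups". The number came from clinical experience, with no formal calculation, and the split between groups is not given.
- **Secondary endpoints** defines the main oncologic outcome: "RFS events include locoregional recurrence, distant recurrence, and death by any cause".
- **Discussion** closes with the aim: "we wish to confirm that minimally invasive breast surgery can be considered as a standard treatment for women with breast cancer", and as a preventive option for women at high risk.
- In the other direction, **Background** calls this a "multicenter prospective exploratory cohort study", and the Discussion concedes selection bias and says "we are planning a randomized controlled trial for the near future".

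**The concern.** The article claims no oncologic superiority for robotic or endoscopic surgery. To become a standard treatment on cancer grounds, the new approach has to be shown not to be materially worse. A log-rank test addresses a different null, that of no difference. Failing to reject it is compatible with equivalence and also with a sizeable excess of recurrences that the study had too few events to detect. Only a confidence bound separates the two.

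The contrast lies within the article. For complications it specifies a margin and an inferiority null; for recurrence, death and new cancers it specifies neither. At stake is whether an uninformative p-value could later be cited in support of cancer safety.

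**Working it through.** **1. The plan's own figure.** The only statistical sample size is the 112 for grade III complications. Inputs from Pre-specified subgroup analysis: reference 34.8%, robotic 17.1%, margin 0.05, one-sided 0.025, power 80%, unpooled Z.

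n per arm = (1.960 + 0.842)² × (0.348×0.652 + 0.171×0.829) / (0.348 − 0.171 + 0.05)² = 56.15.

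Exact binomial enumeration at 56 per arm gives power 0.8004 and an actual level of 0.0265, the level the article reports. So 112 is right for complications. Nothing oncologic enters it.

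**2. Inputs for the oncologic check.**
- From the article: 2000 patients; risk-reducing mastectomy (RRM) share 11.5% or 23.15%. That gives 230 or 463 RRM women, and 1770 or 1537 therapeutic patients.
- Assumed, because the article gives none: conventional-arm 5-year RFS (S₀) of 95, 90 or 85%; minimally invasive share p of 20, 30 or 50%; complete 5-year follow-up; no confounding; two-sided 5% test.

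**3. Full cohort, Schoenfeld approximation.** With N therapeutic patients:

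d = N(1−p)(1−S₀) + Np(1−S₀^HR); z = ln(HR) × √(d·p·(1−p)); chance of a miss = Φ(1.96 − z).

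Example with N = 1537, p = 0.2, S₀ = 0.95, HR 1.5: d = 84.2, z = 1.489, miss = 68%. With N = 1770, p = 0.5: d = 109.8, z = 2.124, miss = 43%.

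| 5-year RFS | HR 1.5 missed | HR 2.0 missed | Deficit in 5-year RFS at HR 1.5 |
|---|---|---|---|
| 95% | 43–68% | 2–24% | 2.4 points |
| 90% | 15–44% | at most 4% | 4.6 points |
| 85% | 5–27% | under 1% | 6.6 points |

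The deficit is S₀ − S₀^1.5, for example 0.95 − 0.926 = 0.024.

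**4. What a bound would show.** If the observed HR is 1, its upper 95% limit is exp(1.96/√(d₀·p·(1−p))) with d₀ = N(1−S₀). At RFS 95% (77–88 events) this is 1.52–1.75; at 90% (154–177 events), 1.34–1.48.

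To exclude an illustrative HR margin of 1.5 with 80% power needs (1.960 + 0.842)² / (p(1−p)·(ln 1.5)²) events: 191 at p = 0.5, 228 at p = 0.3 and 299 at p = 0.2. Expected events reach 191 or 228 only at RFS 85% (231–266 events), and 299 in none of these scenarios.

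**5. If the registry-trial subgroup is the 112 patients (56 v 56).** The same formulas give:
- HR 1.5: d = 6.9, 13.8 and 20.5 at RFS 95, 90 and 85%; missed 92, 89 and 85% of the time.
- HR 2.0: missed 83, 71 and 60% of the time.
- Upper 95% limit at an observed HR of 1: 5.2, 3.2 and 2.6.

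**6. RRM cancer incidence.** Assume a 5-year incidence of 0.5–2% and a minimally invasive share of 30 or 50%. With no difference, 230–463 women give 1.2–9.3 events (230×0.005 to 463×0.02). By exact Fisher power, a tripled incidence is missed 46% of the time (463 women, 2%, 30% share) to over 99% (230 women, 0.5%, 50% share).

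**The case against.** - **A reader might infer that a non-significant result will be declared safe.** No passage says so. Statistical analyses gives no decision rule, and the closing hope in the Discussion names no endpoint. What stands is narrower: the stated test cannot support the oncologic part of that hope.
- **The article limits itself.** It is labelled exploratory, and firm surgical and oncologic evidence is deferred to a later randomised trial. This stands and lowers the weight of the point. It does not remove the tension with an aim to confirm a standard treatment through this study.
- **Intervals for secondary endpoints may be in documents not shown.** Fair; their absence alone would be no finding. The point is the mismatch between the method named and the conclusion sought.
- **A reader might infer that a relevant excess would usually be missed.** That holds only under some assumptions. A doubled hazard would usually be detected in the full cohort, and HR 1.5 is well covered at RFS 85% with a balanced split.
- **A reader might infer that the oncologic comparison is confined to 112 patients.** The article does not say this. The 112 is for robotic against reference on complications; the oncologic subgroup contrast pools endoscopic and robotic. Step 5 is therefore conditional.
- **The 0.05 complication margin might look like a ready-made oncologic margin.** It is not. Five points would tolerate HR 1.5 at RFS of 95% and 90% (2.4 and 4.6 points), and even HR 2.0 at 95% (0.95 − 0.9025 = 4.75 points).

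**Conclusion.** The point holds in this limited form: the only named analysis for RFS, overall survival and cancer incidence is a difference test, and its non-significance cannot support the oncologic part of a standard-treatment conclusion. That does not depend on any assumption about event rates.

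The size does. Across the assumed ranges, the full cohort misses HR 1.5 between 5% and 68% of the time, while HR 2.0 is missed at most 24% of the time. A subset of 112, if used, would say almost nothing about recurrence, and the RRM comparison has too few events for a between-arm safety statement. Separate robotic and endoscopic comparisons would rest on fewer patients than the pooled ones computed here. The exploratory label and the planned trial make this a matter to correct in the wording and analysis, not a fatal flaw.

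**What to change.** In Statistical analyses:

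- For RFS and overall survival, report the hazard ratio and the 5-year difference with two-sided 95% confidence intervals in the full cohort, adjusted for the measured factors that drive choice of surgery. An unadjusted bound from self-selected groups could reassure falsely.
- State that a non-significant log-rank test will not be taken as evidence of oncologic safety.
- Make a not-worse statement only against a margin fixed beforehand and justified on oncologic grounds, not carried over from the complication comparison. Otherwise describe the oncologic results as exploratory or inconclusive.
- For RRM, report cancer incidence per arm with an exact upper 95% limit, and make no between-arm safety claim.
- Treat oncologic results in any subset sized for complications as descriptive only.

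In the Discussion, unless a margin is set, reword the aim to confirm so that it agrees with the exploratory label in Background.

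Cost: wording and a little more analysis, with no new patients. The downside is that the oncologic conclusion may have to be reported as inconclusive.

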**Fig. 1 Fig1:**
[figure not shown]
Flowchart of the prospective cohort study

The inclusion criteria for the patients are as follows: adult women older than 19 with breast cancer or a high risk of breast cancer (patients with *BRCA1/2*, *TP53*, *PALB2* mutations, etc.) who are scheduled for a therapeutic or risk reducing mastectomy and want immediate reconstruction. The PI or a physician delegated by the PI provides information about the study and an adequate opportunity to consider all options to all potential trial participants and obtains signed informed consent forms before enrollment. Patients who plan breast-conserving surgery or who are not candidates for IBR will be excluded. The target number of enrolled patients is 2000.

Patients' clinicopathological factors, including height and weight, will be collected, along with data on surgical results, including photographic and oncological results and cost-effectiveness and patient satisfaction data. The basic characteristics, photographs, and satisfaction of patients will be collected preoperatively using the Breast-Q survey. Patient data will be collected within 6 months of surgery, including clinicopathological factors, surgery results (drainage amount, removal date, and complications), postoperative recovery evaluations, complications and adverse reactions, and cost. Between 6 months and 1 year after surgery, the results of surgery, recurrence, a satisfaction survey, intraoperative console video, and postoperative photographs will be collected. Every 12 months thereafter, data on adjuvant therapy (chemotherapy, radiation therapy, targeted therapy, and endocrine therapy), surgical results, recurrence, adverse events, and other unintended effects of the interventions will be investigated and collected until the end of the study period.

Personal information that can identify the subjects will be kept confidential even after the publication of the study. After enrollment, each participant’s name will be encrypted and replaced with a participant number. The datasets collected from each institution will be accumulated and stored in a designated computer on a central server. Access to that database is restricted to authorized researchers.

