### Stopping criteria

Patients are free to withdraw from the study at any point without limitation. All data collected before the withdrawal will be included. After a withdrawal, no additional data will be collected from that patient. If the PI determines that it is inappropriate to continue the clinical trial, some part or the entire study could be stopped.

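### Ruling out imputation after drop-out leaves the 6–12-month patient scores resting only on women who stayed, which biases the group comparison if leaving depends on how a woman fared

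*Protocol article*

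**What the plan says.** The Statistical analyses section of the protocol article states the rule outright: "No imputation will be performed for subjects who have missing data due to dropping out of the study". For satisfaction and the cost-effectiveness evaluation it lists chi-square or Fisher's exact tests. For continuous variables, "Continuous variables will be examined by t-testing or ANOVA", with rank-based alternatives if needed. All of these use observed values only and adjust for nothing.

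Under Secondary endpoints, the satisfaction outcome is "Patient satisfaction with reconstruction results preoperative (baseline) and 6 to 12 postoperative months". The EQ-5D comes from a "survey 6 months to 1 year after the last surgery", and no preoperative EQ-5D is mentioned.

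Stopping criteria says of women who withdraw: "All data collected before the withdrawal will be included. After a withdrawal, no additional data will be collected from that patient".

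By then much is already on file. Methods/Design (text after Figure 1) has the BREAST-Q survey taken before surgery. Within 6 months of surgery it collects clinicopathological factors, cost and "surgery results (drainage amount, removal date, and complications", among other items.

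**The concern.** A woman who leaves before her 6–12-month questionnaire has a known surgical group, reconstruction type and baseline survey, and a complication record up to the day she left. She has no later score. Under the stated rule and the named tests she simply disappears from the satisfaction and EQ-5D comparisons.

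An unadjusted comparison of the remaining women is sound only if, within each group, leaving is unrelated to the score that would have been given. Severe complications could plausibly affect both staying and satisfaction, and their frequency may differ between surgical groups. For its power calculation, Pre-specified subgroup analysis reports from a previous study that "the rates of grade III complications in the reference group and the robotic group were 34.8% and 17.2%, respectively". If that imbalance recurs here and leaving depends on complications, the group difference is distorted, and the Discussion presents large-scale patient-reported data as a strength of this study.

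A separate matter is whether earlier data from women who leave are kept at all. Stopping criteria includes them, while Statistical analyses says "Data relating to major protocol non-adherence due to patients dropping out of the study will be excluded from the analysis population". Those two statements should be reconciled, but the present point stands even if every earlier value is kept.

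**Working it through.** **The plan's own figure.** The article gives no number for drop-out, satisfaction or EQ-5D. The only related figure is the matched-subgroup sample size of 112. For an adverse event with margin 0.05 and rates 0.348 and 0.171, the size per group is

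n = [0.348×0.652 + 0.171×0.829] × (1.960 + 0.842)² / (0.348 + 0.05 − 0.171)² ≈ 56.15.

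Exact binomial enumeration at 56 per group gives one-sided alpha 0.0265 and power 0.8004, so 112 reproduces. This confirms the rates used as planning inputs. It says nothing about drop-out.

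**Inputs for the check**
- Severe-complication proportion p: 0.348 conventional, 0.171 robotic (Pre-specified subgroup analysis, which gives 17.2% for the previous study and 17.1% for power).
- Retention to the questionnaire: rc after a severe complication, ru otherwise. Not in the article. Assumed rc = 0.50–0.70 and ru = 0.85, the same in both groups.
- Loss of score after a severe complication, d: not in the article. Assumed 10–20 points on a 0–100 scale, with no other difference between groups.

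**Formulas**
- Share with a complication among women who stayed: s = p·rc / [p·rc + (1−p)·ru].
- Full-cohort difference in mean score: (0.348 − 0.171)·d = 0.177·d.
- Complete-case difference: (s conventional − s robotic)·d.

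**Worked case, rc = 0.60, ru = 0.85**
- Conventional: 0.2088 / (0.2088 + 0.5542) = 0.274.
- Robotic: 0.1026 / (0.1026 + 0.7047) = 0.127.
- Difference in shares: 0.1466 against 0.177, which is 17.2% too small. With d = 15, that is 2.20 points instead of 2.65.

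**Range, ru = 0.85**

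| rc | s conventional | s robotic | Difference in shares | Understated by |
|---|---|---|---|---|
| 0.70 | 0.305 | 0.145 | 0.160 | 9.5% |
| 0.60 | 0.274 | 0.127 | 0.147 | 17.2% |
| 0.50 | 0.239 | 0.108 | 0.131 | 26.1% |

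In points, the bias in the difference runs from (0.177 − 0.160)×10 ≈ 0.2 to (0.177 − 0.131)×20 ≈ 0.9. The conventional mean alone is overstated by (0.348 − 0.305)×10 ≈ 0.4 to (0.348 − 0.239)×20 ≈ 2.2 points.

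The percentages do not depend on d. Nor do they need rates this high: at 20% versus 10% complications, 60%/85% retention gives 0.150 − 0.073 = 0.077 against 0.100, about 23% too small. They describe the part of the difference that runs through complications. A further constant difference between groups would leave the bias in points unchanged and alter the percentage.

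**Other drop-out patterns** (rates 0.348 and 0.172, d = 10, full-cohort difference 1.76)

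| Drop-out after complication / otherwise | Complete-case difference |
|---|---|
| 10% / 10% | 1.76 (no bias) |
| 20% / 10% | 1.66 |
| 50% / 10% | 1.25 |
| 10% / 20% | 1.86 |
| 10% / 30% | 1.96 |
| 30% / 10% in conventional only; 10% / 10% in robotic | 1.21 |
| 30% / 10% in robotic only; 10% / 10% in conventional | 2.09 |

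The sign therefore depends on a pattern that the article does not give.

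**The case against.** The strongest reply is that the harm is assumed. No part of the article gives a drop-out rate or ties leaving to complications or to surgical group. A reader might infer that the rule in itself shrinks the difference and flatters the group with more complications. The documents do not support that: equal drop-out gives no bias and the opposite pattern reverses it.

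A reader might also infer that the plan forbids any use of what is known about women who leave. It forbids imputation, and only for data missing through drop-out. Weighting is not excluded, although none is planned. A woman who stays in the study but skips a questionnaire is not covered by the sentence at all.

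Nor should the 34.8% and 17.2% be read as what the plan expects in the whole cohort. They come from a previous study, serve as power inputs for the matched subgroup, and say nothing about the endoscopic group.

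The size is modest. In a simulation of the 60%/85%, 15-point case with 1000 women per group (a split that the article does not state), the bias of 0.45 points was under half the standard error of 0.95. Standardising on complication status recovered the full-data value (2.66, against 2.21 complete-case), but it had to, because missingness was made to depend on that status alone. Only a difference in means was examined, although categorical tests are named as well.

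Finally, these are secondary outcomes of a study that calls itself exploratory and concedes selection bias in the choice of surgery. Further sensitivity analyses may sit in an analysis plan that is not shown.

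All of this limits the claim and its weight. It does not remove the point: the rule is stated rather than left open, and not knowing the drop-out pattern is a reason not to make complete-case the only stated analysis.

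**Conclusion.** The point holds in conditional form. The stated rule and the named tests make the 6–12-month BREAST-Q and EQ-5D comparisons complete-case. The comparison is unbiased if drop-out is unrelated to outcome, understated if women with severe complications leave more often, and overstated under the reverse pattern.

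The range of about 10–26%, or 0.2–0.9 points on a 0–100 scale, rests on three assumptions: the planning complication rates, 50–70% versus 85% retention in both groups, and a 10–20-point complication effect. None of the retention or score figures comes from the article, and the point values do not carry over to an EQ-5D index on another scale. This is a worthwhile, inexpensive improvement to secondary outcomes; it does not touch the primary endpoints.

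**What to change.** In Statistical analyses, limit the no-imputation sentence to the complication and survival endpoints, which stay on observed data and censoring. For the 6–12-month patient scores, among women eligible for the scale concerned:

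- Use multiple imputation by surgical group, or inverse-probability-of-response weighting. Base it on baseline BREAST-Q, age, BMI (height and weight are collected), reconstruction type, institution, and the worst Clavien-Dindo grade recorded up to withdrawal or day 180, whichever comes first. The grade must be defined this way because collection stops at withdrawal.
- Report the complete-case result as a sensitivity analysis.
- Add a sensitivity analysis for scores missing not at random.
- Tabulate response by surgical group and complication status, so readers can see which pattern occurred.

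The cost is revised wording and some extra analysis, with no new data. The approach relies on scores being missing at random given the recorded variables, a weaker condition than the unadjusted complete-case comparison needs. Two limits remain: the complication record is cut short for women who leave before day 180, and no baseline EQ-5D is stated, so the correction will be weaker for that outcome.
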